## Abstract

**Background:**

In 2015, the stillbirth rate after 28 weeks (late gestation) in Australia was 35% higher than countries with the lowest rates globally. Reductions in late gestation stillbirth rates have steadily improved in Australia. However, to amplify and sustain reductions, more needs to be done to reduce practice variation and address sub-optimal care. Implementing bundles for maternity care improvement in the UK have been associated with a 20% reduction in stillbirth rates. A similar approach is underway in Australia; the Safer Baby Bundle (SBB) with five elements: 1) supporting women to stop smoking in pregnancy, 2) improving detection and management of fetal growth restriction, 3) raising awareness and improving care for women with decreased fetal movements, 4) improving awareness of maternal safe going-to-sleep position in late pregnancy, 5) improving decision making about the timing of birth for women with risk factors for stillbirth.

**Methods:**

This is a mixed-methods study of maternity services across three Australian states; Queensland, Victoria and New South Wales. The study includes evaluation of ‘targeted’ implementer sites (combined total approximately 113,000 births annually, 50% of births in these states) and monitoring of key outcomes state-wide across all maternity services. Progressive implementation over 2.5 years, managed by state Departments of Health, commenced from mid-2019. This study will determine the impact of implementing the SBB on maternity services and perinatal outcomes, specifically for reducing late gestation stillbirth. Comprehensive process, impact, and outcome evaluations will be conducted using routinely collected perinatal data, pre- and post- implementation surveys, clinical audits, focus group discussions and interviews. Evaluations explore the views and experiences of clinicians embedding the SBB into routine practice as well as women’s experience with care and the acceptability of the initiative.

**Discussion:**

This protocol describes the evaluation of the SBB initiative and will provide evidence for the value of a systematic, but pragmatic, approach to strategies to reduce the evidence-practice gaps across maternity services. We hypothesise successful implementation and uptake across three Australian states (amplified nationally) will be effective in reducing late gestation stillbirths to that of the best performing countries globally, equating to at least 150 lives saved annually.

**Trial registration:**

The Safer Baby Bundle Study was retrospectively registered on the ACTRN12619001777189 database, date assigned 16/12/2019

## Background

Stillbirth is a tragic event for the woman, her partner, family and friends, as well as the healthcare professionals involved. Stillbirth imparts significant costs across the health system and society [1]. Every day in Australia six babies are stillborn, amounting to more than 2000 deaths a year [2]. For Aboriginal and Torres Strait Islander and some migrant and refugee communities (South Asian [3] and African [4]), stillbirth rates are often doubled [5].

In 2015, the stillbirth rate after 28 weeks’ gestation in Australia was 35% higher than countries with the lowest rates globally [6]. The average annual rate reduction at that time was 1.4%, ranking Australia 15th across high-income developed countries. Since then reductions in late gestation stillbirth rates have steadily improved [7, 8]; however, more can be done to reduce stillbirths in line with comparable countries [6]. A co-ordinated national approach to reducing practice variation and addressing areas of sub-optimal care provision is needed for further reductions in stillbirth. High quality clinical audits [9] suggest around 20 – 30% of late gestation stillbirths could be avoided with better care [10].

Working in partnership with parents, healthcare professionals, professional colleges, parent advocacy organisations, and government agencies, the Centre of Research Excellence in Stillbirth (Stillbirth CRE) identified key evidence-practice gaps in stillbirth prevention [11]. In early 2018, the Australian Senate convened a committee to inquire and report on the future of stillbirth research and education in Australia. The committee’s report [12] made a number of key recommendations encompassing improving the quality of antenatal care to address stillbirth in Australia. In response the government provided additional funding to the Stillbirth CRE to support national rollout of the Safer Baby Bundle (SBB), recognizing this key initiative to ensure that pregnant women are provided with high quality, evidence-based antenatal care that reduces the risk of stillbirth [13].

Care bundles like the SBB are used frequently in health care with the aim of improving patient outcomes. They typically contain three to five evidence-based elements designed to formalise care and/or reduce practice variation [14]. Care bundles in stillbirth prevention in the UK have shown benefit [15, 16]. The Scottish Maternity and Children Quality Improvement Collaborative (MCQIC) has been associated with a stillbirth rate reduction of 22.5% since 2014 [16, 17] and the Saving Babies Lives Care Bundle (SBLCB) evaluation in England showed a 20% reduction [15]. The four care elements included in the SBLCB were: smoking monitoring and cessation strategies; monitoring fetal growth; reduced fetal movements; and effective fetal monitoring in labour [15].

### The Safer Baby Bundle

The SBB is modelled on the SBLCB [15] with modifications made through extensive consultation with the project’s partners and collaborators, national experts, professional bodies, parent advocates and a survey of lead clinicians across Australian maternity hospitals [18]. The survey highlighted gaps in care for each of the proposed elements. The SBB, which is founded on evidence-based recommendations for Australia and New Zealand [19–24], aims to address these gaps.

The five SBB elements address commonly identified evidence practice gaps: 1) supporting women to stop smoking in pregnancy, 2) improving detection and management of fetal growth restriction (FGR), 3) raising awareness and improving care for women with decreased fetal movements (DFM), 4) improving awareness of maternal safe going-to-sleep position in late pregnancy, 5) improving decision making about the timing of birth for women with risk factors for stillbirth. Specific recommendations for the five elements are detailed in the SBB Handbook and Resource Guide [25], which has been endorsed by peak professional bodies, parent advocacy organisations, Departments of Health partners, and was made publicly available in October 2019.

Implementation of the SBB is supported by a comprehensive package of evidence-based and collaboratively developed resources. These include: best practice recommendations; implementation tools including clinical checklists and management algorithms; key performance indicators and audit; an educational program for healthcare providers (eLearning and face-to-face training); information and educational resources for women and their families; and a communications and awareness campaign.

In January 2019, the Stillbirth CRE, in partnership with the Stillbirth Foundation Australia, Still Aware and Departments of Health across Queensland (QLD), Victoria (VIC) and New South Wales (NSW), received funding to implement and evaluate the SBB across these three states. Commencing from mid-2019, implementation of the SBB was undertaken in partnership with these three state Departments of Health. Commencement dates, implementation strategies and approaches vary across jurisdictions but the intent for all is to progressively embed the SBB within existing care over a 12-24month implementation period (post-launching).

Subsequent to the original development of this study, the SARS-COV-2 (COVID-19) was identified by the World Health Organization as a global health emergency and pandemic [26]. Isolation measures were first introduced in Australia in March 2020. Since then maternity care has changed due to restrictions imposed by the COVID-19 pandemic. For example, telehealth has replaced routine antenatal visits and women are reporting increased self-monitoring. At this time the overall impact of COVID-19 restrictions on implementation and evaluation of the SBB are uncertain. There is growing concern that stillbirth rates may increase during the pandemic as suggested by recent evidence from the UK [27]. The original protocol for this study has been amended here to extend the implementation time period to account for launch delays (for QLD) and disruptions to implementation activities, and to add measures to assess the indirect impact of COVID-19 restrictions on stillbirth and other important maternal and neonatal outcomes.

We report here the protocol for the evaluation of the SBB initiative and the state-led quality improvement programs supporting implementation across maternity services in NSW, QLD and VIC.

## Methods

### Study aims and objectives

The overall purpose of this study is to determine the impact of implementing the SBB on Australian maternity services and perinatal outcomes. The primary aim is to (1) demonstrate the effectiveness of the SBB in reducing late gestation stillbirth rates (28 weeks’ gestation or more). The study also aims to: (2) understand the processes and contextual factors influencing implementation success; (3) determine the impact of the SBB on change in awareness, knowledge, behaviours and experiences around providing or receiving antenatal care for healthcare professionals and women respectively; (4) to undertake an economic evaluation of the SBB.

The study’s primary objective is to compare stillbirth rates at 28 weeks’ gestation or more across Australian maternity settings pre and post implementation of the SBB. Secondary objectives include:
Using routinely collected perinatal data to assess the endpoint effectiveness of the SBB for other important clinical outcomes, including any unintended consequences such as increased unnecessary intervention and preterm birthTo explore variations in the provision of antenatal care influencing disparities in stillbirth rates for Aboriginal and Torres Strait Islander, migrant and refugee, and rural and remote womenTo evaluate the coverage, acceptability, feasibility, fidelity, and sustainability of the SBB initiative and its implementation across settings and for different stakeholdersTo explore indirect process and contextual factors influencing antenatal care provision in relation to the SBB elements due to COVID-19 pandemic restrictions through interviews and surveys with project leadsTo explore the views and experiences of women and maternity healthcare professionals with antenatal care in relation to the five SBB elements utilising surveys, focus groups and interviewsTo estimate the cost-effectiveness of the SBB compared to standard care.

### Study design

This study is a mixed methods, multi-centre, ‘before and after’ evaluation of the implementation of the SBB in three health jurisdictions. The study design is pragmatic to account for differences across jurisdictions for the level of implementation support provided and commencement times. VIC commenced implementation in June 2019, NSW launched in February 2020 and although QLD commenced baseline data collection from January 2020 their launch planned for March 2020 was delayed to October 2020 due to COVID-19. The study ‘implementation period’ (which includes pre and post implementation data collection as part of the implementation strategy) will therefore run for 2.5 years, followed by a 2 year post-implementation (maintenance phase). Data collection for final evaluation is anticipated to end by December 2023, with analysis and final reporting completed by June 2024. Given the uncertainties posed by the COVID-19 pandemic, there may be further delays in opportunities for data collection and implementation activities, however, this does not affect the framework for evaluation outlined here.

### Study setting

The SBB initiative, education program and all associated resources have been promoted and made accessible state-wide to all hospitals and healthcare professionals providing maternity care in NSW, VIC and QLD. The initial rollout of the SBB in these jurisdictions is managed through state-specific SBB implementation programs providing targeted support to hospitals recruited to and engaged with these programs. Thus, while all public and private maternity hospitals will be exposed to the SBB initiative through access to eLearning and resources, initially state-wide uptake and implementation will be driven by participation in formal quality improvement programs. These programs provide the opportunity for an in-depth evaluation of such approaches by facilitating collection of comprehensive process and impact data.

This study includes all public and private hospitals providing maternity care in NSW, VIC and QLD. Sites are grouped by level of implementation support into: (1) ‘targeted’ implementers, maternity hospitals recruited to and engaged with state-led SBB implementation programs; (2) ‘non-targeted’ implementers, all other maternity hospitals in each state. For ‘targeted’ implementers, participation was open to maternity hospitals across the three jurisdictions, with those who expressed an interest in joining recruited. Up to August 2020, 83 sites/hospitals were recruited (VIC- 23 sites across all 6 health regions, NSW- 25 sites across 4 Local Health Districts and QLD- 36 sites across 17 Hospital & Health Services). These sites account for approximately half of all births in these states.

Change in stillbirth rates and other important clinical outcomes will be described by state-wide routinely collected perinatal data for all births. Comparisons will be described by state, ‘targeted’ versus ‘non-targeted’ implementers, and between ‘targeted’ implementers. The study population includes women with a singleton pregnancy (28 weeks’ gestation or more) without lethal fetal anomalies attending for antenatal care.

For other aims and objectives, evaluations described here for process, impact, outcome and economic measures apply specifically to ‘targeted’ implementers (unless otherwise stated). The study population for these includes all women attending for antenatal care and healthcare professionals providing maternity care at ‘targeted’ implementer sites.

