### Evaluation design

A mixed-methods approach will be used to assess the processes, impacts and outcomes for the SBB initiative. Change in rates for the primary clinical outcome, stillbirth rate at 28 or more weeks, will compare the pre-implementation rate (including longer term trends over 15 years) with the rate in the 2 year post-implementation period (Time Point 2 (TP2)), using routinely collected perinatal data (see Fig. 1.) To allow for differences in commencement dates between jurisdictions and implementation disruptions due to COVID-19 restrictions, a 2.5 year implementation period is proposed. Key process and impact measures will be compared pre- (baseline) and post-implementation at evaluation TP1 including data from surveys of women and healthcare professionals, clinical audits and implementation process data. A survey of maternity service leads will be undertaken at TP1 (post-implementation) to assess changes in maternity services resource use, level of implementation and the influence of leadership, governance and workforce culture on implementation.

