Element 2: improving detection and management of FGR	Process	Proportion of women with documented risk assessment for FGR at first antenatal care visit.
		Proportion of women (at any gestation) identified as at risk of FGR whose care was escalated as per the FGR care pathway^a^.
		Proportion of women with SFH measurement taken and plotted on growth chart at each antenatal visit from 24 weeks’ gestation.
		Proportion of stillbirths from 28 weeks’ gestation where substandard care for FGR detection or management are identified
	Maternity services impact	Proportion of term births with undetected FGR defined as severely growth restricted singletons (less than 3rd centile) undelivered at 40 weeks’ gestation (missed FGR)
	Outcome	Proportion of singleton babies delivered for suspected FGR at 37 weeks’ gestation or more who have a birthweight >25th centile.
Element 3: raising awareness and improving care for women with DFM	Process	Proportion of women provided with DFM information by 28 weeks’ gestation.
	Maternity services impact	Proportion of women with singleton pregnancies who have a CTG commenced within 2 hours of presenting (in person) at the maternity service with DFM, from 28 weeks’ gestation.
		Proportion of stillbirths from 28 weeks’ gestation where substandard care for DFM reporting or management are identified
		Percentage of women at 28 weeks’ gestation or more who attend a maternity service within 12hrs of DFM concern.
		Proportion of women with singleton pregnancies who present with DFM who undergo induction of labour or elective caesarean section before 39 weeks’ gestation for DFM as the only indication.
Element 4: improving awareness of maternal safe going-to-sleep position in late pregnancy	Process	Proportion of women who, by 28 weeks’ gestation, were given the information brochure on safe going-to-sleep position in late pregnancy.
	Impact	Proportion of women who report safe sleep practices after 28 weeks’ gestation.
		Proportion of women after 28 weeks’ gestation who can describe safe sleep practices (going to sleep on their side).
Element 5: improving decision making about the timing of birth for women with risk factors for stillbirth	Process	Proportion of women assessed for stillbirth risk factors at first antenatal care visit
		Proportion of women reassessed for stillbirth risk factors at 34-36+6 weeks’ gestation
	Impact	Proportion of women who report being involved as much as they wanted in decision-making about timing of birth

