	Outcome	Proportion of women with singleton pregnancies who undergo induction of labour or elective caesarean section before 39 weeks’ gestation.

Abbreviations: *FGR* Fetal growth restriction, *SFH* Symphyseal-fundal height, *DFM* Decreased fetal movements, *CTG* Cardiotocography

^a^PSANZ/Stillbirth CRE FGR care pathway for singleton pregnancies [21]

**Impact measures** will assess the SBB programs effect on participants and include; healthcare professionals reported change in awareness, knowledge, attitudes, behaviours, and/or practices with implementation of the SBB and more broadly through use of the educational program; women’s reported change in awareness and behaviours in response to the five elements of care, as well as changes in experience with and quality of care received; maternity service reported change in service responsiveness and utilisation, Table 1.

**Outcome measures** focus on the endpoint effectiveness of the SBB program and demonstrate changes in clinical outcomes. The **primary clinical outcome** is stillbirth at 28 weeks’ or more gestation in singleton pregnancies without lethal fetal congenital anomalies. Secondary clinical outcomes will be collected from routinely collected perinatal data and include important maternal and new-born outcomes (including rates of obstetric intervention), Table 2.

**Table 2 Tab2:** Key clinical outcomes

Clinical Outcomes	Measure	
Primary outcome	Stillbirth at 28 weeks’ or more gestation in singleton pregnancies without lethal fetal congenital anomalies	
Secondary outcomes	Fetal/Neonatal	Stillbirth; 20 weeks’ or more gestation; 28 weeks’ or more gestation; 37 or more weeks’ gestation; associated with substandard care factors (undetected FGR, poor DFM reporting or management); cause specific (PSANZ classification^a^)
		Neonatal death; early (within 7 days of birth) or late (within 7-28 days of birth)
		Neonatal hypoxic ischaemic encephalopathy (mild, moderate, or severe grading- ANZNN criteria^b^)
		Small for gestational age; birthweight < 10^th^ centile; birthweight < 3^rd^ centile
		Neonatal seizures
		Preterm birth; early (birth before 32 weeks) or late (birth before 37 weeks)
		Early term birth (birth 37-38 weeks)
		Admission to nursery; special care and/or intensive care; length of stay
		Need for respiratory support (defined using ANZNN criteria^b^)
		Early and late onset neonatal infection (defined using ANZNN criteria^b^)
	Maternal	Induction of labour

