#### Non-identifiable electronic extract of routinely collected perinatal data

Approval will be sought through the relevant state perinatal data collection custodians to access and analyse routinely collected population-based surveillance system data covering all births in NSW, VIC and QLD public and private hospitals over the study time period (covering 15 years’ pre-implementation to 2 years’ post-implementation). This non-identifiable electronic data will be extracted from each of the participating jurisdictions at yearly intervals throughout the duration of the project.

Monitoring and timely reporting of any unintended harm as a result of SBB implementation, such as increased unnecessary intervention and preterm birth, is essential [32]. Annual analysis of routine data extracts throughout both implementation and maintenance phases will allow for benchmarking of selected indicators. Reporting of comparisons for stillbirth rates and other important clinical outcomes will be for both ‘targeted’ and ‘non-targeted’ implementers. These comparisons will describe the effect of state-wide uptake of SBB components over time and consider any indirect impacts on antenatal care provision due to COVID-19 restrictions by jurisdiction.

Requested data items include: maternal demographics and medical history; previous pregnancy complications and birth outcomes; current pregnancy details; labour and birth outcomes; neonatal outcomes; and hospital demographics. Routinely collected hospital service utilisation data for each participating hospital will also be obtained as part of the SBB dataset. These data are routinely collected and reported to state health departments as part of minimum reporting requirements for activity-based funding.

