#### Clinical audits and implementation process data

Jurisdictions may undertake and report a series of audits to assess process evaluation measures including missed cases of FGR, reporting of DFM and women birthing at term (measures such as risk assessment and management according to risk, smoking cessation support). Through these audit and feedback, benchmarking of key performance indicators will flag priority areas for practice change. ‘Targeted’ implementers will report on a standard set of process, impact and outcome measures for each of the five elements as part of their quality improvement strategies to implement. This data is important to understand the fidelity of the implementation strategies and sites will provide these implementation process data through the respective health departments (CED, CEC, SCV).

High quality clinical audit of all stillbirths to identify substandard care factors will be promoted through provision of the IMproving Perinatal Mortality Review and Outcomes Via Education (IMPROVE) program [33]. The data collection tool recommended by PSANZ [30] will be recommended for use across all participating maternity services to inform the standard clinical review of all stillbirths.

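### Missed FGR is compared only at targeted sites, baseline against TP1, so a change in it could not be told from background drift or COVID-19 effects

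*Protocol article*

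**What the plan says.** The protocol article sets two scopes in Study setting. For clinical outcomes: "Change in stillbirth rates and other important clinical outcomes will be described by state-wide routinely collected perinatal data for all births". For these it adds: "Comparisons will be described by state, ‘targeted’ versus ‘non-targeted’ implementers, and between ‘targeted’ implementers". For its other aims and objectives, the next paragraph says: "evaluations described here for process, impact, outcome and economic measures apply specifically to ‘targeted’ implementers (unless otherwise stated").

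Evaluation design gives the timing for the second group: "Key process and impact measures will be compared pre- (baseline) and post-implementation at evaluation TP1".

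Table 1 (Evaluation measures) places missed FGR at the level of maternity services impact, under Element 2, and words it so: "Proportion of term births with undetected FGR defined as severely growth restricted singletons (less than 3rd centile) undelivered at 40 weeks’ gestation (missed FGR"). Table 2, which lists the clinical outcomes, does not contain it. The section on clinical audits and implementation process data names it again, this time as a process measure: "Jurisdictions may undertake and report a series of audits to assess process evaluation measures including missed cases of FGR".

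The routine perinatal extract is described as "covering all births in NSW, VIC and QLD public and private hospitals over the study time period", from 15 years before implementation to 2 years after.

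Table 1 also lists, under Element 5 and at the level of outcome: "Proportion of women with singleton pregnancies who undergo induction of labour or elective caesarean section before 39 weeks’ gestation". This measure is not in Table 2 either.

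**The concern.** Missed FGR is the Table 1 indicator that shows most directly whether severely growth-restricted babies are still being missed at term. Read together, the sections give it one comparison: targeted sites, before against after. That comparison has no pre-implementation trend and no concurrent sites. If missed FGR was already falling, or if care changed because of the pandemic, the before-after difference would contain those changes, and nothing in the stated comparison could remove them.

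The protocol gives reason to expect both. Its own late stillbirth rate was falling before the bundle (Sample size and data analysis), and its Background reports that telehealth replaced routine antenatal visits after March 2020, inside the implementation period. The weakness also looks avoidable, because the protocol plans a state-wide extract over many years for the Table 2 outcomes.

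**Working it through.** **1. The plan's own figure.** The article gives no precision or power for missed FGR. Its only such figure is for stillbirth: 95% power for 1.9 against 2.4 per 1000. With two periods of 2 × 113,000 = 226,000 births, SE = √[(0.0024×0.9976 + 0.0019×0.9981)/226,000] = 0.000138, and power = Φ(0.0005/0.000138 − 1.96) = 95.2%. The figure reproduces but says nothing on missed FGR.

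**2. Which rule governs missed FGR.**
- Level: impact (Table 1); absent from Table 2.
- Sites: targeted only (Study setting). No other section states an exception for it.
- Timing: baseline and TP1 (Evaluation design).
- Source: audits that are optional for jurisdictions, plus the standard measure set that targeted sites report.
- Trend or non-targeted comparison: none stated.

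**3. Whether the extract could supply it.** The definition needs plurality, gestational age at birth and birthweight centile. Table 2 already uses all three: a singleton primary outcome, preterm and early term birth, and birthweight below the 3rd centile. The extract section lists only broad item groups, so availability is a strong inference and not a stated fact.

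**4. What drift alone could do (illustration).** The article gives neither a base rate nor a drift for missed FGR, so both are assumed. Inputs: no bundle effect; 2.5 years between periods (the stated implementation period); n = 113,000 births per period (one year at targeted sites, as stated); base rate p₁ of 1% or 2%; yearly relative fall d of 1%, 2% or 4%. For scale, the stillbirth fall from 2.7 to 2.4 per 1000 over one three-year step is 1 − (2.4/2.7)^(1/3) = 3.9% a year.

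Formula: p₂ = p₁(1 − d)^2.5; SE = √[p₁(1−p₁)/n + p₂(1−p₂)/n]; chance of a significant fall = Φ((p₁ − p₂)/SE − 1.96).

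Example with p₁ = 1% and d = 4%: p₂ = 0.903%, difference 0.097 points, SE 0.0408 points, ratio 2.38, chance Φ(0.42) = 66%.

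| Yearly fall | Apparent ratio | Base 1% | Base 2% |
|---|---|---|---|
| 1% | 0.975 | 9% | 13% |
| 2% | 0.951 | 22% | 40% |
| 4% | 0.903 | 66% | 92% |

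A steeper assumed fall of 5% a year, with an assumed 92% of births at term (113,000 × 0.92 = 103,960), gives 1% × (1 − 0.95^2.5) = 0.120 points against SE = √(2×0.01×0.99/103,960) = 0.0436 points, or 2.8 standard errors.

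**5. If small audits are the source.** With an assumed 2,000 births per period, the same formula gives 3.0% to 6.5% over the whole table. Drift would then seldom be significant, but a real change of the same size would be found just as seldom.

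**6. What a concurrent comparison does.** If both site groups drift by the same factor (1 − d)^2.5, the ratio of their before-after ratios is 1.0, so the shared drift cancels.

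**The case against.** The strongest reply is that the targeted programs exist to give in-depth process and impact data, and that restricting such measures to engaged sites is ordinary in an implementation evaluation. The article also provides for annual benchmarking of selected indicators from routine data, which might include missed FGR. This stands in part. However, the selection is not given, and benchmarking during the implementation and maintenance phases adds no pre-implementation years. Nor is this only detail left to a fuller document: the article itself fixes sites, timing and source for this class of measure.

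Four stronger readings are tempting, and the documents do not support them.

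- **Planned birth before 39 weeks has the same defect.** Table 1 labels it an outcome, so the baseline-against-TP1 sentence does not cover it. The secondary objectives, the extract section and the sample size section place unnecessary or obstetric intervention in routine data, reported for both site groups and analysed similarly to the primary endpoint. Table 2 has induction, elective caesarean and early term birth. Only its exact place is unclear: the Table 2 induction and caesarean items have no gestation limit, and early term birth mixes planned with spontaneous birth.
- **Missed FGR may be absent where a state does not audit.** The audit section also commits targeted sites to reporting a standard set of measures for each of the five elements.
- **Drift will be read as a bundle effect.** It could be. At a 1% base and a 1% to 2% yearly fall, the chance is only 9% to 22%, even at full volume.
- **The data are already held.** Custodian approval is still to be sought.

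The remedy also has limits. All hospitals have access to the bundle's eLearning and resources, and targeted sites volunteered. A targeted against non-targeted contrast may therefore dilute or confound a real effect.

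**Conclusion.** The point holds for missed FGR. As written, it is an uncontrolled comparison of two time points at targeted sites, and a change in it could not be attributed to the bundle rather than to background drift or pandemic changes in care. How far it could mislead is unknown, because the documents give neither a base rate nor a trend. The 9% to 92% range, the 2.8 standard errors and the audit figures are illustrations on assumed rates. The conclusion does not rest on them; it rests on the stated scope and timing, and on the strong inference that the extract holds the needed fields.

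For planned birth before 39 weeks, all that remains is a scope to reconcile between Study setting, Table 1 and Table 2.

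**What to change.** In Study setting and in the section on clinical audits, state that missed FGR will also be derived from the state perinatal extract, for all hospitals, by year and site group, from 15 years before implementation to 2 years after. Analyse it like the Table 2 outcomes, with the pre-implementation trend and the targeted against non-targeted change. Keep audits for items the extract does not hold. Confirm with the data custodians that plurality, gestation and birthweight centile are supplied, and give missed FGR one level, since it is now called both process and impact.

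List induction or elective caesarean before 39 weeks with the routine-data outcomes in Table 2.

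The cost is a little more analysis of data already being requested, and it may reduce audit work. Because non-targeted sites are partly exposed and targeted sites volunteered, read the site-group contrast together with the 15-year trend. The trend addresses long-running drift but not a pandemic break; the contrast addresses shock shared by both groups but may understate or distort a real effect.
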